#### Follow-up plan

Utilizing an aggregation cross design, referencing the grouping methodology of the Baby Connectome Project (BCP) by UNC/UMN in the USA (12), participants were categorized into 9 sub-cohorts based on the age at initial enrollment, each having varying sampling density and age spans (Table 1). Each of the first three sub-cohorts enrolled 536 participants, while sub-cohorts 4–9 each enrolled 268 participants, totaling 3,216 participants. Each participant was followed up 3–4 times, yielding data from 11,256 participant—visits. Moreover, the follow-up intervals for sub-cohorts 1–3 and 4–9 were 3 and 6 months, respectively, ensuring sufficient sampling density during the first year, which is critical for rapid development in language and socio-emotional skills. Oversampling was strategically implemented during milestones of language and socio-emotional development and periods prone to scan failures (before the age of 3). Considering the low cooperation levels of infants and potential dropouts, 3,847 participants were recruited to ensure the acquisition of high-quality data from 3,216 subjects (Figure 1).

**Table 1 T1:** Cohort design and follow-up time planning schedule.

**Aggregated cross design**						
**Cohort number**	**Number**	**Follow-up**				**Note**
		**First**	**Second**	**Third**	**Fourth**	
1	536	0	3	6	9	High-density sampling: once every 3 months
2	536	1	4	7	10	
3	536	2	5	8	11	
4	268	10	16	22		Medium-density sampling: every 6 months
5	268	6	12	18		
6	268	9	15	21		
7	268	12	18	24		
8	268	15	21	27		
9	268	24	30	36		
Total	3,216	Number of Participant—visits: 11,256			
Target number	3,847	Considering the failure rate of magnetic resonance imaging and the dropout rate of the cohort, the effective enrollment was guaranteed to be >11,256 cases				

**Figure 1 F1:**
[figure not shown]
Aggregated cohort follow-up time planning schedule.

The study protocol encompasses questionnaires, behavioral assessments, and brain structure and function examinations from the perinatal period of children through the age of 3 years, complemented by whole-exome sequencing. Basic information about the pregnant women and their partners was retrospectively collected at the time of enrollment.

The items and contents of the data collected at the time of entry and at different follow-up age points are detailed in Table 2 (Detailed descriptions of the scales and tasks used during the follow-up visits can be found in the Supplementary material). The study collects brain images, EEG data, data about the environment, and data about the genes of infants and young children, and evaluate cognitive development, emotional development, and language development of infants and young children.

**Table 2 T2:** Timeline for follow-up programs by age group.

**Test content**	**Tool name**	**Age group (month)**						
		**Perinatal period**	**0–1**	**2–6**	**7–12**	**13–18**	**19–24**	**25–36**
**Brain structure and function**								
Brain MRI	/		√	√	√	√	√	√
**Electrophysiological monitoring of brain waves**								
EEG	/		√	√	√	√	√	√
**Behavioral assessments**								
Developmental level	Griffiths Development Scales-Chinese Edition (GDSC) (19)		√	√	√	√	√	
Intelligence	Wechsler Intelligence Scale for Children—Fourth Edition (WPPSI-IV) (20)							√
**Maternal and Parenting Issues—Parental Questionnaire**								
Basic Information	Background questionnaire	√	√	√	√	√	√	√
Family parenting environment	Index of Child Care Environment (ICCE) (21)					√	√	√
Parenting Stress	Parenting Stress Index-Short Form (PSI-SF) (22)		√	√	√	√	√	√
Childbirth experience	Postpartum Experiences Questionnaire within 3 months (PPQ) (23)		√	√				
Work-family conflict	Work-Family Conflict Scale (24)		√	√	√	√	√	√
Pregnancy-Life events	Pregnancy Life Events Questionnaire (PLQ) (25)	√						
Pregnancy stress	Pregnancy Stress Scale (PPS) (26)	√						
Depression	Self-Rating Depression Scale (SDS) (27)		√	√	√	√	√	√
Anxiety	State-Trait Anxiety Inventory for Young Adults (STAI-Y) (28)		√	√	√	√	√	√
Sleep quality	Pittsburgh Sleep Quality Index (PSQI) (29)	√						
Postpartum depression	Edinburgh Postnatal Depression Scale (EPDS) (30)		√	√	√			
Breastfeeding Self-Efficacy	Breastfeeding Self-Efficacy Scale-Short Form (BSES-SF) (31)		√	√				
Mother-infant bonding	Maternal-Infant Bonding Scale (MIBS) (32)				√			
Mother-infant attachment	Maternal Postnatal Attachment Scale (MPAS) (33)		√	√	√			
Parenting style	Parenting Styles and Dimensions Questionnaire (PSDQ) (34)							√
Family functioning	Family Assessment Device (FAD) (35)		√					
Collaborative parenting	Co-Parenting Questionnaire (36)							√
**Children Issues—Parental Questionnaire**								
Baby sleep	Brief Infant Sleep Questionnaire (BISQ) (37)		√	√	√	√	√	√
Childlike temperament	Chinese Toddler Temperament Scale (CTTS) (38)					√	√	√
Social emotions	Ages & Stages Questionnaires: Social-Emotional, 2nd Edition (ASQ:SE-2) (39)		√	√	√	√	√	√
Language development	Putonghua Communicative Development Inventory-Words and Gestures“ (PCDI: Words and Gestures) (40)				√	√		
	Chinese Communicative Development Inventories: Words and Sentences” (CCDI: Words and Sentences) (41)						√	√
Behavioral assessment	Child Behavior Checklist (CBCL) (42)					√	√	√
Autism spectrum disorder screening	Modified Checklist for Autism in Toddlers, Revised with Follow-up(The M-CHAT-R/F) (43)					√	√	√
Use of electronic devices	Seven-in-Seven Screen Exposure Questionnaire (44)						√	√
**Behavioral experiments**								
Psychological theory	Theory of Mind (ToM) (45)							√
Executive function/self-control	Head Toes Knees Shoulders (HTKS) (46)							√
Emotion-related self-regulation, etc	Emotional Stroop Task (47)							√
**Behavioral observations**								
Negative emotion regulation, social emotion	Still Face Experiment (48)			√	√			
Language expresses social emotions	Mother–Infant Interaction (49)			√	√	√		
Executive control	Strange Situation Test (50)						√	
Executive control	Frustration Tolerance Task (51) + Delay of Gratification Task (52)							√
**Blood**								
Genetic and exposome	/	√						

#### Brain imaging data

At each follow-up visit, the data of the brain magnetic resonance examination in the non-sedated state of the subjects were collected, including skull structure MRI (sMRI), resting-state fMRI, dMRI sequence and multi-parametric MRI (MTP) scans for a total of 40 min. All MRI data were acquired on a 3T scanner (uMR 890, United Imaging) with a 64-channel head coil. The scanning protocol was as follows: Structural MRI: High-resolution T1w/T2w images (0.8 mm isotropic) using AI-assisted compressed sensing (ACS) (53), achieving 37.8% time reduction compared to BCP protocols (5). Resting-state fMRI: Single-shot EPI (TR = 800 ms, 1.8 mm isotropic) with multiband factor = 8 and field-map-based distortion correction. Diffusion MRI: 72 directions with 3 shells (*b* = 500/1,000/3,000) and dual phase-encoding, utilizing incremental acquisition for sampling uniformity (54). Multi-parametric MRI (MTP): Gradient-echo sequences generating PDw/T1w/T2w images and quantitative maps (PD/T1/T2/QSM) through dual-TR/dual-flip-angle design. Automated slice positioning (Easy Scan) was used to standardize scan planning. For sleeping subjects, supplemental scans (fMRI with reversed phase-encoding; dMRI at *b* = 1,500/2,000/2,500) were added to mitigate geometric distortions. The detailed MRI acquisition protocol is summarized in Table 3.

**Table 3 T3:** The parameter list of the multi-MRI protocol (12, 54, 55).

**Sequence**		**Matrix**	**FoV (mm)**	**Resolution (mm)**	**TE (msec)**	**TR (msec)**	**Slices/orientation**	**Time (min:sec)**	**Acceleration strategy**
Localizer		115 × 144	300 × 300	2.6 × 2.08 × 4	1	2.7	1/Sag	00:10	-
T1-weighted		320 × 300	256 × 240	0.8 × 0.8 × 0.8	2.9	7.4	208/Sag	03:44	ACS, × 3.3
T2-weighted		320 × 300	256 × 256	0.8 × 0.8 × 0.8	452	3,000	208/Sag	04:09	ACS, × 3.8
Field Map		116 × 116	209 × 209	1.8 × 1.8 × 1.8	2.46	501.2	72/Axial	00:58	-
BOLD Rest Ref PA		116 × 116	209 × 209	1.8 × 1.8 × 1.8	35	800	72/Axial	00:25	Multi-band = 1
BOLD Rest PA		116 × 116	209 × 209	1.8 × 1.8 × 1.8	35	800	72/Axial	06:25	Multi-band = 8
DWI b0 AP		140 × 140	210 × 210	1.5 × 1.5 × 1.5	77.5	3,000	92/Axial	00:40	Multi-band = 4
DWI	PA, *b* = 500, 1,000, 3,000	140 × 140	210 × 210	1.5 × 1.5 × 1.5	77.5	3,014	92/Axial	04:29	Multi-band = 4, 3 shells, 72 directions
	AP, *b* = 1,500, 2,000, 2,500	140 × 140	210 × 210	1.5 × 1.5 × 1.5	77.5	3,014	92/Axial	04:29	
MTP		192 × 192	230 × 190	0.8 × 0.8 × 1.6	20.76	36.8	70/Axial	7:10	ACS, × 4
**Contingent on the baby continuing to sleep**									
BOLD Rest Ref AP		116 × 116	209 × 209	1.8 × 1.8 × 1.8	35	800	72/Axial	00:25	Multi-band = 1
BOLD Rest AP		116 × 116	209 × 209	1.8 × 1.8 × 1.8	35	800	72/Axial	06:25	Multi-band = 8
DWI	PA, *b* = 500, 1,000, 3,000	140 × 140	210 × 210	1.5 × 1.5 × 1.5	77.5	3,014	92/Axial	04:29	Multi-band = 4, 3 shells, 72 directions
	AP, *b* = 1,500, 2,000, 2,500	140 × 140	210 × 210	1.5 × 1.5 × 1.5	77.5	3,014	92/Axial	04:29	

#### EEG examination

EEG data were collected at each follow-up visit. EEG recordings are conducted using a 32-channel actiCAP active electrode system (Brain Products GmbH) with GreenTek GT5 conductive gel, positioned according to the standardized 10-10 international system (56). Signals are amplified via a BP actiCHamp Plus amplifier and monitored in real-time using BrainVision Recorder software. Electrode impedances are maintained below 5 kΩ throughout sessions via automated DRT quality control software (MATLAB R2018a runtime environment). All infants (0–3 years) are tested in naturally alert states, verified through continuous behavioral observation. One operator manages device calibration and event marking, while a second observer documents infant behaviors (e.g., head movements, vocalizations) .

The EEG Experimental Tasks Include:

(1) Resting State (Resting): The test involves the acquisition of a 5-min resting state.(2) Three Language Tasks: (1) Infant Speech Perception Ability (FFR/Oddball): The test involves presenting two types of auditory stimuli in a pseudo-random manner. (2) Infant Vocabulary Semantic Development in Social Scenarios (SceneWord): The test involves observing infants' responses to auditory stimuli after they view pictures with situational and environmental information. (3) Development of Infant Syntactic Ability (Syntax): The test content is the continuous input of auditory stimuli in a regular pattern.(3) Two Emotion Tasks: (1) Emotion Classification (Face Emotion): The test involves rapidly presenting images or stimuli representing different emotions. (2) Empathy with Natural Stimuli (Empathy): The test requires the infants to watch a silent animated cartoon.

To ensure that sufficient data can be collected for this task modality, the research team has decided to adopt a rotation method based on the age of the participants and the categories of the multimodal tasks. The rotation requirement is that in each experiment, 2 tasks are selected from the language tasks, 1 task is selected from the emotion tasks, and the resting state task, which is mandatory, is added. In total, there are 4 tasks. The estimated duration of the tasks is ~30–40 min.

#### Behavioral assessment

(1) Griffiths Development Scales—Chinese Edition (GDSC) (57): Griffith assessment was performed during the follow-up of preterm infants after discharge. Griffiths scale is a standardized assessment scale for children aged 0–8 years whose mother tongue is Chinese and which has Chinese norms. The scale is divided into two parts: 0–2 years old and 0–8 years old, the 0–2 years old part is composed of 5 domains: “A Movement”, “B Individual-Society”, “C Language”, “D Hand-eye Coordination” and “E Performance”, and the 0–8 years old part adds “F Practical Reasoning Domain” on this basis. When the developmental quotient DQ < 70, it indicates developmental delay; when DQ ≥85, it indicates normal development.(2) Wechsler assessment: this study uses the WPPSI—IV (58) to assess the child's intelligence level. Five scores are calculated from the questionnaire, namely the Verbal Comprehension Index (VCI), Visual Spatial Index (VSI), Working Memory Index (WMI), Fluid Reasoning Index (FRI), and Processing Speed Index (PSI). Then, the scores of different ability areas will be summarized based on the questionnaire data to obtain the Full Scale IQ (FSIQ) score, which comprehensively reflects the overall intellectual level of children. Different intellectual level intervals are divided according to the FSIQ.

#### Parent-questionnaire

An electronic questionnaire was designed on the WeChat public account platform. After parents follow and register, the system will push the parent questionnaire of the corresponding age group for parents to fill in. The electronic questionnaires were divided into two main categories: maternal and parenting issues, and children's issues, as detailed in Table 2.

(1) The Maternal and Parenting Issues Questionnaire primarily investigates the family parenting environment , maternal parenting stress, pregnancy and postpartum events, postpartum emotional state of mother and work-family relationships. It further explores the impact of these environmental factors on children's brain development.

Among them, the Family Parenting Environment Survey uses the Index of Child Care Environment (ICCE) (21): the scale has a total of 13 questions and includes family interaction, external contact, avoiding scolding and social support. The total score of the scale ranges from 0 to 13 points, and the higher the score, the better the child's nurturing environment. According to the distribution of population scores, the ICCE total score was divided into four groups: the worst family environment group (≤ 10 score), the lower-middle group (11 score), the upper middle group (12 score), and the best group (13 score).

(2) The Children's Related Issues Questionnaire mainly investigates the sleep of infants, childlike temperament, social emotions, language development, behavioral assessment, autism spectrum disorder screening and use of electronic devices. Among them, (1) the Ages and Stages Questionnaires-Social-Emotional (the 2nd edition) (39), focuses on the emotional development and mental health of infants and young children. There are two types of screening results for ASQ—SE: below the boundary value and equal to or higher than the boundary value. The latter indicates that the child's development is in line with his or her monthly development level. (2) Language development: a. Infant and child communication development questionnaire: vocabulary and gesture short form. This scale was jointly revised by the University of Michigan, the National University of Cork, Ireland, and Peking University in 2008. The vocabulary scale of the scale has a total of 219 items, which contains most of the vocabulary used by normal Chinese children, such as: person, food, animal, drink, body, parts, as well as verbs, adverbs, quantifiers, and tenses. The “Vocabulary and Gesture Short Table” examines the items that children “don't understand”, “understand”, and “can speak”. “don't understand” gets 0 points, and “understand” and “can speak” get 1 point each. b. The Children's Communication Development Questionnaire: Vocabulary and Sentence Short Tables. It examines items of whether children “can't speak” or “can speak” and “can speak” items, “Can't speak” gets 0 points, “Can speak” gets 1 point.(3) The M-CHAT-R/F (43) (Modified Checklist for Autism in Toddlers, Revised with Follow-up) is a screening tool used to assess the risk of autism spectrum disorder in toddlers aged 16 −30 months. The screening process consists of two steps: the first step is an initial questionnaire, and the second step is a follow-up interview. The questionnaire is completed by the child's parents or main caregivers based on the child's actual behavior.

#### Behavioral experiments

(1) Psychology Theory Task (45) (36 months of age and above)—tests the child's psychotheoretical ability.(2) Head, Foot, Knee, and Shoulder (HTKS) Task (46) (25-month-old and older)—tests the child's executive function/self-control.(3) Emotional Stroop Task (47) (25-month-old and older)—tests children's ability to self-regulate emotionally.

#### Behavioral observations

(1) Still Face (48) (3–12 months old)—This task is used to test the negative emotion regulation and social emotion of infants. It consists of three stages: face-to-face interaction, still-face episode, and reunion. Measuring infants' ability to achieve interactions by regulating emotional expression reflects infants' early goal—oriented social competence.(2) Mother–Infant Interaction (49) (6–18 months of age)—This task tests for verbal expression and social emotion. This semi-structured observation records 10 min of mother–child interaction. During the observation, parents are encouraged to interact with their children in a normal way. This observational experiment can reflect a number of indicators, such as maternal sensitivity, infant social referencing, dyadic contingent responses, etc.(3) Strange Situational Test (50) (21–27 months old)—Inhibition/Control Ability: Three strangers interacted with children in the presence and absence of their mothers, respectively, to assess the infant's attachment security.(4) Frustration Tolerance & Delayed Gratification Task (51) (30–42 months old)—To test inhibition/control ability: The first paradigm was adapted from the classic marshmallow experiment, using snacks and crayons to observe children's self-control. The second paradigm presents the child with a situation in which the goal is blocked. In these tests, toddlers' patience time, coping strategies, and parental responses will be classified and coded.

#### Genetic and exposome testing

At the time of enrollment, 2 ml of blood from each parent and child were drawn once, whole exome sequencing and exposome were performed, and multivariate statistical methods were used to analyze genes and biomarkers related to brain, early language and emotional development. In addition, through the deep sequencing of the whole genome, a variety of genetic analysis methods, including candidate-gene analysis, whole-gene analysis, and multi-gene risk combination analysis methods, will be used to explore the molecular mechanisms of brain structure, function, connections, and the developmental trajectory of language and emotion, and elucidate the precise mechanism of gene expression during human brain development.

### Outcomes

#### Primary outcome

##### Cohort and data goals

This study will create a 0–3-year-old infant brain development assessment cohort. This study aims to gather comprehensive “gene – environment - image - behavior” multimodal data, with a focus on high-quality collection. The data will be used to establish a solid foundation for research on infants brain development, and the data integrity rate is expected to be at least 90% across all data categories.

##### Brain development mapping

Using advanced magnetic resonance imaging (MRI) and electroencephalogram (EEG) technologies, we will precisely map the early brain development of infants and determine the developmental patterns of infant brain functions. This includes determining, through technologies such as image recognition, the brain development curves of infants with age, as well as the normal volume ranges of different brain regions at each age group. It also involves recording the growth patterns of brain structures such as the hippocampus and prefrontal cortex, and the development of neural connections. By analyzing the data, we will map the brain development trajectories of Chinese children and identify the critical periods of brain development.

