## Introduction

Brain development is currently the most concerned—about frontier field of brain and cognitive science in the world. Brain development during the fetal period is very sensitive to environmental influences. Transcriptional programs in the fetal brain regulate complex developmental processes that ultimately shape the functional structure of the adult brain. Thus, alterations in the intrauterine environment can have far-reaching and long-lasting effects on neurodevelopment (1, 2). Epidemiological data suggest that severe maternal infection during pregnancy is associated with an increased risk of neurodevelopmental and neuropsychiatric disorders, including schizophrenia, bipolar disorder, attention deficit hyperactivity disorder (ADHD), developmental delay, cognitive dysfunction, anxiety/depression, and autism spectrum disorder (ASD), among others (3, 4). In addition, infants experience dramatic changes in brain structure, function, and connections from birth. Synapses are produced in large numbers on the microstructure, and pruning and apoptosis related to the environment and experiences are produced (5); At the macroscopic level, the appearance of magnetic resonance is greatly changed due to the rapid development of axonal myelination. The cortex is significantly thickened, dilated, and folded, and the functional integration is significantly enhanced (6). Long-term follow-up studies have revealed that the cognitive levels reached in infancy and early childhood continue to affect many aspects of physical and mental health, wealth, and longevity in the middle and late adulthood (7). However, currently, our understanding of the mechanisms of these complex brain development processes and the deleterious effects of maternal inflammation on brain development in infants and young children is still limited. Although the micro research carried out in the field of basic neuroscience has reached preliminary conclusions, in order to evaluate the risk factors of brain development and predict the outcome of brain development, it is still necessary to study the brain mechanism of development, especially the map of brain dynamic development, at the macro level. Magnetic Resonance Imaging (MRI), characterized by its non-ionizing radiation and excellent spatial resolution for cerebral tissue, enables the acquisition of multi-parametric information. Furthermore, advanced sequences facilitate functional and biochemical metabolic analyses, thereby providing objective biomarkers for evaluating neonatal brain development and diagnosing cerebral injuries (8). Electroencephalogram (EEG), especially the event-related potential (ERP) technique, can be used to non-invasively explore the cognitive processes of infant speech recognition, language comprehension, phonological awareness, recognition memory, and facial emotion recognition (9, 10). Researchers can, through experimental paradigms specifically designed for different age groups, explore ERP components, characteristics, origins, and influencing factors of language and social-emotional development in infants and toddlers aged 0–3 years (11). These imaging techniques, combined with brain image modeling, can reveal the mysteries of early brain development and the impact of maternal inflammation. Due to the limitations of technology and research objects, it is very difficult to study infant brain development. Under the promotion of the Human Connectome Project (HCP) in the United States, the leading Infant Connectome Project (BCP) has been successfully carried out (12), which has led to a boom in research on infant brain development. Since the 13th Five-Year Plan, China has been taking brain science as a national strategy. Artificial intelligence has been regarded as “a strategic technology to lead this round of scientific and technological revolution and industrial transformation”.

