#### Data analysis

##### Cohort and data objectives

Conduct an integrity assessment of the “gene-environment-electroencephalogram (EEG)—imaging-behavior” multimodal data for the included cohort of infants and toddlers aged 0–3 years. Calculate the integrity of core data such as questionnaire data, gene data, and children's behavior data, with an integrity rate of at least 90%. For data with high noise levels such as brain magnetic resonance imaging (MRI) and EEG, the integrity rate should be ≥85%, and the overall integrated integrity should be ≥80%. Examine the reasons for missing data. For completely random missing data of different types, use methods such as multiple imputation, k-nearest neighbors (KNN) imputation, the Generative Adversarial Imputation Network (GAIN) algorithm, and expert judgment filling to supplement the data. Filter gene data through the Genome Analysis Toolkit (GATK), annotate it with ANNOVAR, and screen high-quality loci through the Hardy-Weinberg Equilibrium (HWE) test. Remove outliers from environmental data regarding inflammatory indicators during pregnancy, pregnancy complications, and family parenting scales. Process MRI structural images using Free Surfer/FSL and functional magnetic resonance imaging (fMRI) using Statistical Parametric Mapping (SPM) for imaging data. Preprocess EEG data using EEGLAB. Transform behavior data into Z-scores. Present demographic characteristics through descriptive statistics. Use the chi-square test/analysis of variance to compare baseline differences among subgroups such as gender and gestational age to ensure the balance of the cohort and lay the foundation for subsequent analyses.

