##### Mapping of brain development atlas

Based on the preprocessed MRI and EEG data, we use FreeSurfer to quantify the volumes of brain regions such as the hippocampus and prefrontal cortex, and calculate the normal range of brain region volumes related to age. Calculate and plot the curves of the volumes of specific brain regions of children by gender through non-linear functions as they change with age, and identify the critical windows of development for specific brain regions in infants. Extract time-frequency features such as α/β wave power from EEG data, construct a functional connectivity matrix, and analyze the development pattern of the resting-state EEG network through graph theory analysis and independent component analysis. Use canonical correlation analysis to explore the coordinated development relationship between the volume of MRI brain regions and the functional connectivity of EEG. At the same time, conduct piecewise regression on longitudinal data, detect the mutation points of the brain development rate, and verify its correlation with the development scores in terms of intelligence, cognition, and behavior, so as to comprehensively depict the dynamic development trajectory of brain structure and function.

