### Construction of high-precision brain function map

This study will construct a map of brain function and structure from birth to early childhood and capture the dynamic changes in brain structure and function through multimodal neuroimaging techniques, including MRI and EEG. MRI will be particularly useful for visualizing structural changes, while EEG will provide insights into functional connectivity and electrical activity. Time series analysis methods will be applied, processing sequential imaging data collected from birth to early childhood to reveal key time nodes and developmental pathways in brain development. We will develop and optimize image processing algorithms, specifically for the particularity and complexity of infant brain imaging data, to ensure the accuracy and effectiveness of data analysis.

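### Regional volumes behind the primary age curves and normal ranges (0–36 months) are assigned to FreeSurfer without any age or infant qualification, so age-dependent segmentation error could be confounded with growth

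*Protocol article*

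**What the plan says.** Under Primary outcome, Brain development mapping, the protocol article commits to "determining, through technologies such as image recognition, the brain development curves of infants with age, as well as the normal volume ranges" in each age group, and to finding critical periods of development. That section points only to image recognition as the means and names no software.

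The tool is named in the Data analysis section. Under Cohort and data objectives: "Process MRI structural images using Free Surfer/FSL". Under Mapping of brain development atlas: "we use FreeSurfer to quantify the volumes of brain regions such as the hippocampus and prefrontal cortex, and calculate the normal range". The same paragraph plans sex-specific non-linear curves of regional volume against age, and a piecewise regression to "detect the mutation points of the brain development rate". Neither section gives an age range, an infant variant, or a check of segmentation by age.

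Two other places bear on this. The Introduction says that in infancy "the appearance of magnetic resonance is greatly changed due to the rapid development of axonal myelination". The Discussion, under Construction of high-precision brain function map, says "We will develop and optimize image processing algorithms, specifically for the particularity and complexity of infant brain imaging data". The Brain imaging data section describes the structural scans as "High-resolution T1w/T2w images (0.8 mm isotropic", and Table 3 lists a single T1w and a single T2w setting with no variation by age.

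**The concern.** A regional volume is the output of a segmentation, and a segmentation that relies on tissue intensity depends on contrast. The article itself says the appearance of the images changes greatly over the ages studied. If the method is not suited to each age, its error can change with age, and age is the horizontal axis of the primary curves and ranges.

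Such an error does not average out with more children. It would also be hard to see afterwards, because a smooth shift in segmentation error looks like a smooth change in growth. Where the shift slows or stops, the slope of the measured curve changes. A piecewise regression could place a break there and the study could report it as a critical period.

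The volumes are used again as inputs to the risk model (Construction of infant brain development models). Brain volume and cortical thickness are also related to CRP and IL-6 in the secondary analyses. The authors evidently see that infant images need special handling, but that recognition does not reach the sections that fix how the primary outcome is measured.

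**Working it through.** **1. The plan's own visit count (Table 1).** Sub-cohorts 1–3: 3 × 536 × 4 = 6,432 visits. Sub-cohorts 4–9: 6 × 268 × 3 = 4,824 visits. Sum: 11,256, which agrees with the table. An MRI is planned at each visit.

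**2. Where those scans fall by age.** Visits scheduled at 0–11 months are all twelve visits of sub-cohorts 1–3 (12 × 536 = 6,432), plus month 10 of sub-cohort 4, month 6 of sub-cohort 5 and month 9 of sub-cohort 6 (3 × 268 = 804). Total 7,236; 7,236 / 11,256 = 64.3%. Of these, 6 × 536 = 3,216 (28.6% of all visits) fall before 6 months.

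By the age bands of Table 2:

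| Age band (months) | Planned visits | Share |
|---|---|---|
| 0–1 | 1,072 | 9.5% |
| 2–6 | 2,948 | 26.2% |
| 7–12 | 3,752 | 33.3% |
| 13–18 | 1,340 | 11.9% |
| 19–24 | 1,340 | 11.9% |
| 25–36 | 804 | 7.1% |

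The 360 children enrolled so far were scanned at a mean age of 3.28 weeks (Table 4), the youngest end of this range. These figures show when scans occur. They do not show that segmentation errs.

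**3. The method statements side by side.**

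| Section | Stated means of measurement |
|---|---|
| Brain development mapping (primary outcome) | image recognition |
| Cohort and data objectives (analysis) | FreeSurfer/FSL |
| Mapping of brain development atlas (analysis) | FreeSurfer |
| Construction of high-precision brain function map (Discussion) | algorithms developed for infant images |

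The article does not say how the last relates to the two before it.

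**4. How an error that changes with age enters a growth estimate.** Let true growth over a window be G, and let the relative segmentation error be e0 at its start and e1 at its end. Then measured growth = (1 + G)(1 + e1)/(1 + e0) − 1. A constant error (e0 = e1) cancels out of relative growth; only a change in the error matters.

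The documents give no values, so the following is illustration on assumed inputs: G = 50% or 100%, e1 = 0, and e0 of 5, 10 or 20% in either direction.

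| e0 | Measured if G = 50% | Measured if G = 100% |
|---|---|---|
| −20% | 1.5/0.80 − 1 = 88% | 2/0.80 − 1 = 150% |
| −10% | 1.5/0.90 − 1 = 67% | 2/0.90 − 1 = 122% |
| −5% | 1.5/0.95 − 1 = 58% | 2/0.95 − 1 = 111% |
| 0 | 50% | 100% |
| +5% | 1.5/1.05 − 1 = 43% | 2/1.05 − 1 = 90% |
| +10% | 1.5/1.10 − 1 = 36% | 2/1.10 − 1 = 82% |
| +20% | 1.5/1.20 − 1 = 25% | 2/1.20 − 1 = 67% |

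Early under-reading exaggerates growth and early over-reading hides it. The table shows sensitivity only; it does not estimate what will happen in this cohort.

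**The case against.** The strongest reply is that the article gives a software name and nothing about its configuration. Nothing in it says that an adult-configured stream will be used, that FreeSurfer is unsuitable for infants, or that changing contrast biases its volumes. The Discussion's infant-specific processing may be meant to work before or within FreeSurfer: the atlas section starts from data that have already been preprocessed, so the two statements can be read together. T2w images may also already be in use, because the Brain imaging data section counts them as structural MRI and the analysis section sends structural images through FreeSurfer/FSL. Version numbers and quality thresholds are details that a condensed article may leave to a fuller document.

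Most of this stands, and it limits the point. A reader might infer that contrast maturation will be read as brain growth. The documents do not support that: neither the sign nor the size of any error can be derived, and the Introduction also describes real cortical thickening and folding at these ages. A reader might also infer that the analysis ignores the T2w images, or that the Discussion and the analysis text contradict each other outright. Neither follows.

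What the reply does not remove is that the analysis text makes a positive choice of instrument for a primary outcome, without qualification, across ages at which the article says image appearance changes greatly. The link to the promised infant-specific processing is left to the reader. That goes beyond an omitted version number.

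**Conclusion.** The point holds as a risk created by the stated method. Taken as written, FreeSurfer/FSL without an age condition supplies the volumes for the primary ranges and curves at 0–36 months, and 64.3% of planned scans fall before 12 months. Age-dependent segmentation error could therefore be confounded with growth, in either direction and of a size the documents do not give, and could produce false change points.

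This rests on one general premise that the article does not state: that segmentation accuracy depends on tissue contrast. It also assumes that the infant-specific processing is not applied in the volume analysis, which the text leaves open. A difference in error between exposure groups is a further possibility, but only if image maturity differs between them. Table 4 is split by sex and does not show this.

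The change should be made before volumes are derived for the ranges and curves. Confidence is medium.

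**What to change.** In Mapping of brain development atlas, replace the unqualified FreeSurfer with an infant-specific, age-appropriate segmentation pipeline that uses the T1w and T2w images already acquired. An infant-adapted FreeSurfer stream would qualify. Lock one version and apply it identically in both exposure groups.

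Check segmentation accuracy within each Table 2 age band, for example against manual segmentation of a sample of scans; naming a pipeline does not by itself show that its error is stable over age. Report normal ranges and change points only for regions and ages that pass.

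Reconcile the four sections compared above, so that the primary outcome, the two analysis sections and the Discussion name the same method and say where the infant-specific processing enters.

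The cost is pipeline set-up, some reprocessing and the accuracy check. No new scans are needed. Some regions or ages may have to be reported as not available.
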